**Secondary and exploratory outcome variables***			
The different variables being part of the primary safety composite outcome will even be studied individually in the form of exploratory analyses.			
Stillbirth defined as intrauterine foetal death of a fetus that was alive at time of randomisation	Dichotomous (yes, no)	ICD-10 O36.4	SPR
Neonatal death of a live born child that dies days 0–27, not including accidents	Dichotomous (yes, no)	SNQ 2101, 2103	SNQ, SCB, the Cause of Death Register
Apgar score <4 at 5 min	Dichotomous (yes, no)	SNQ 421, SPR “Apgar5”	SNQ, SPR
pH <7.00 or base deficit >15 mmol/L in the umbilical artery	Dichotomous (yes, no)		SNQ, SPR
Severe birth asphyxia	Dichotomous (yes, no)	ICD-10 P21.0	SNQ, SPR
Hypoxic ischaemic encephalopathy II–III	Dichotomous (yes, no)	ICD-10 P91.6B or C or tick box	SNQ
Intracranial haemorrhage	Dichotomous (yes, no)	ICD-10 P10, P52	SNQ
Neonatal convulsions	Dichotomous (yes, no)	ICD-10 P90	SNQ
Therapeutic hypothermia	Dichotomous (yes, no)	ICD-10 P80.8, P80.9, DV034	SPR, SNQ
Meconium aspiration syndrome	Dichotomous (yes, no)	ICD-10 P24.0	SNQ, SPR
Mechanical ventilation within first 72 hours	Dichotomous (yes, no)	Procedure code DG021, DG022, DG002	SNQ
Neonatal pneumonia	Dichotomous (yes, no)	ICD-10 P23	SNQ
Neonatal sepsis	Dichotomous (yes, no)	ICD-10 P36	SNQ
NICU admission >48 hours	Dichotomous (yes, no)		SNQ
Further outcomes for the child			
Obstetric brachial plexus injury	Dichotomous (yes, no)	ICD-10 P14.0, P14.1, P14.3, P14.8, P14.9	SNQ, SPR
Admission to the NICU	Dichotomous (yes, no)		SNQ
Time at NICU	Continuous (days and hours)		SNQ
Treatment for hypoglycaemia	Dichotomous (yes, no)	ICD-10 P70.3 P70.4A-B, P70.8, P70.9	SNQ, SPR
Readmission after delivery due to the child’s health until day 27 after delivery	Dichotomous (yes, no)		SNQ
Healthy person accompanying sick person (mother stays at the hospital due to need of care for the newborn) until day 27 after delivery	Dichotomous (yes, no)	ICD-10 Z76.3	SPR
Apgar score <7 at 5 min	Dichotomous (yes, no)	SNQ 241, SPR “Apgar5”	SNQ, SPR
Further outcomes for the mother within 12 weeks from delivery if not specified otherwise			
Vaginal delivery (spontaneous vs instrumental)	Dichotomous (yes, no)	Tick box Spontaneous vaginal ICD-10 O80 Instrumental vaginal ICD-10 O81 Procedure code MAF00, MAF10, MAF96, MAC23 MAE00, MAE03, MAE20, MAE96	SPR
Maternal death until 42 days after delivery that can be connected to the pregnancy	Dichotomous (yes, no)	ICD-10 O95, O97	SPR, SCB, the Cause of Death Register
Maternal death after 42 days after delivery that can be connected to the pregnancy	Dichotomous (yes, no)	ICD-10 O96	SPR, SCB, the Cause of Death Register
Pre-eclampsia	Dichotomous (yes, no)	ICD-10 O14, O15,	SPR
Gestational (pregnancy-induced) hypertension without significant proteinuria	Dichotomous (yes, no)	ICD-10 O13, O16	SPR
Precipitate labour	Dichotomous (yes, no)	ICD-10 O62.3	SPR
Hypertonic, incoordinate and prolonged uterine contractions	Dichotomous (yes, no)	ICD-10 O62.4	SPR
Uterine rupture	Dichotomous (yes, no)	ICD-10 O71.0, O71.1, Procedure code MCC00	SPR
Hysterectomy in connection with delivery	Dichotomous (yes, no)	ICD-10 O82.2, Procedure code MCA33	SPR
Cardiac arrest	Dichotomous (yes, no)	ICD-10 I46	SPR, the National Patient Register
Obstetric shock	Dichotomous (yes, no)	ICD-10 O75.1	SPR
Other severe maternal morbidity defined as admission to intensive care unit	Dichotomous (yes, no)	ICD-10 ZV049	SPR, hospital charts, the National Patient Register
Thrombosis, pulmonary embolism	Dichotomous (yes, no)	ICD-10 O22.3, O87.1, O87.3, I82.2, I82.8, I82.9, I26	SPR, the National Patient Register, Prescribed Drug Register
Obstetric embolism	Dichotomous (yes, no)	ICD-10 O88	SPR, Prescribed Drug Register
Umbilical cord prolapse	Dichotomous (yes, no)	ICD-10 O69.0, P02.4	SPR
Vaginal delivery within 24 hours (VD24)	Dichotomous (yes, no)	As above within 24 hours after start of induction	SPR
Vaginal delivery within 48 hours (VD48)	Dichotomous (yes, no)	As above within 24 hours after start of induction	SPR
Stroke	Dichotomous (yes, no)	ICD-10 I61.X, I63.X	SPR, the National Patient Register
Emergency or crash caesarean section	Dichotomous (yes, no)	ICD-10 O82.1	SPR
Indication for instrumental vaginal delivery or delivery by caesarean section		Foetal distress ICD-10 O.68.9, O36.3, Infection ICD-10 O75.3, O98.8, O98.9, Failure to progress ICD-10 O62.0-2, O62.8-9, Maternal distress during labour and delivery ICD-10 O75.0	SPR
Shoulder dystocia	Dichotomous (yes, no)	ICD-10 O66.0	SPR
Labour dystocia	Dichotomous (yes, no)	ICD-10 O.62.0-1, O62.8-9	SPR
Use of oxytocin	Dichotomous (yes, no)	DT036, DT037	SPR
Hypertonic, incoordinate and prolonged uterine contractions	Dichotomous (yes, no)	ICD-10 O62.4	SPR
Heavy vaginal bleeding before or during delivery	Dichotomous (yes, no)	ICD-10 O46, O67	SPR
Placental abruption	Dichotomous (yes, no)	ICD-10 O45	SPR
Number and reasons of visits and phone calls to the hospital in the outpatient group (balloon catheter expulsion, planned visit after 24 hours, PROM, pain, vaginal bleeding, contractions, impaired urination, foetal movements, delivery before reaching the hospital, other)			eCRF, SPR, the National Patient Register and regional registries as for example, VEGA (Vårddatabas för Enskilda patienter, Grupper och Analyser) in the Western Healthcare region
Need of additional induction method	Dichotomous (yes, no)	ICD-10 O61.X	eCRF, SPR
Infection (before, during, after delivery)	Dichotomous (yes, no)	ICD-10 O75.3, O85, O86, O91, O98, and see below	SPR, the National Patient Register, Prescribed Drug Register
Chorioamnionitis	Dichotomous (yes, no)	ICD-10 O41.1, SNQ 303	SPR, SNQ,
Urinary tract infection	Dichotomous (yes, no)	ICD-10 O86.2	SPR, the National Patient Register, Prescribed Drug Register
Endometritis	Dichotomous (yes, no)	ICD-10 O85.9, O86.1 O86.3, O86.8	SPR, the National Patient Register, Prescribed Drug Register
Wound infection	Dichotomous (yes, no)	ICD-10 O86.0	SPR, the National Patient Register, Prescribed Drug Register
Sepsis	Dichotomous (yes, no)	ICD-10 A41	SPR, the National Patient Register, Prescribed Drug Register
Fever during delivery	Dichotomous (yes, no)	ICD-10 O75.2	SPR
Fever postpartum	Dichotomous (yes, no)	ICD-10 O86.4	SPR
Need and method of pain relief during delivery		ICD-10 ZXH50, ZXH40, ZXH10, SN999	SPR
Episiotomy	Dichotomous (yes, no)	Tick box (left, median, right) Procedure code TMA00	SPR
Grades 3 or 4 perineal laceration	Dichotomous (yes, no)	Tick box sphincter, rectum ICD-10 O70.2, O70.3, MBC33	SPR
Perineal laceration	Dichotomous (yes, no)	Tick box, ICD-10 O70	SPR
Amount of postpartum bleeding	Continuous (mL)		SPR
Postpartum bleeding >1000 mL	Dichotomous (yes, no)	ICD-10 O72	SPR
Transfusion	Dichotomous (yes, no)	Procedure code DR029, DR030, DR036-039	SPR
Breastfeeding at discharge from hospital	Dichotomous (yes, no)		SPR
Breastfeeding at follow-up visit to the midwife at 8–12 weeks postpartum	Dichotomous (yes, no)		SPR
Readmission after delivery due to the mother’s health	Dichotomous (yes, no)		SPR, the National Patient Register
Experience of delivery	Continuous 1–10 Categorical		SPR
Postnatal depression	Dichotomous (yes, no)	ICD-10 F53.X	SPR
Time variables			
Time from start of induction to second stage of delivery	Continuous (hours, minutes)		SPR
Time from start of induction to delivery	Continuous (hours, minutes)		SPR
Duration of stay at the hospital	Continuous (hours, minutes)		SPR
Duration of stay at the hospital before delivery	Continuous (hours, minutes)		SPR
Duration of stay at the hospital after delivery	Continuous (hours, minutes)		SPR
Descriptive outcomes for the outpatient group only			
Delivery within 30 and 60 min from admission to hospital	Dichotomous (yes, no)		SPR
Caesarean section within 60 min from admission to hospital	Dichotomous (yes, no)		SPR
Arrival at the hospital by ambulance	Dichotomous (yes, no)		Ambureg
Delivery before reaching the hospital	Dichotomous (yes, no)		SPR

* The final statistical analysis plan will be set prior to data lock and define which variables will be studied as secondary vs exploratory variables.

Ambureg, the Swedish Ambulance Register; ICD-10, International Statistical Classification of Disease and Related Health Problems, 10th revision; OPTION, Outpatient Induction; PROM, prelabour rupture of the membranes; SCB, Statistics Sweden; SNQ, the Swedish Neonatal Quality Register; SPR, the Swedish Pregnancy Register.

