**Primary outcome 2 is the efficacy variable defined as proportion of vaginal birth in the two groups**			
Caesarean section	Dichotomous (yes, no)	Tick box ICD-10 O82 Procedure code MCA00, MCA10, MCA20, MCA30, MCA33, MCA96	SPR
Vaginal delivery (spontaneous and instrumental)	Dichotomous (yes, no)	Tick box Spontaneous vaginal ICD-10 O80 Instrumental vaginal ICD-10 O81 Procedure code MAF00, MAF10, MAF96, MAC23 MAE00, MAE03, MAE20, MAE96	SPR

ICD-10, International Statistical Classification of Disease and Related Health Problems 10th revision; NICU, neonatal intensive care unit; OPTION, Outpatient Induction; SCB, Statistics Sweden; SNQ, the Swedish Neonatal Quality Register; SPR, the Swedish Pregnancy Register.

**Table 3 T3:** Secondary and exploratory health outcome variables in the OPTION trial

Variable	Type	Description	Source

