### Power calculation

Non-inferiority will be tested with a two-sided 95% CI and 80% power. Calculating with 2.8% (based on data from the SPR 2014–2018^5^) for the primary composite outcome in outpatients and 2.3% in inpatients and a 5% drop-out rate, 8891 women need to be randomised to achieve a probability ≥0.80 that the upper limit of a two-sided 95.7% CI for the difference in primary outcome will be less than the non-inferiority margin 1.5%. The vaginal delivery rate was 88% in a group of women fulfilling the eligibility criteria (SPR, 2014–2018^5^). Assuming a vaginal delivery rate of 90% in the outpatient arm, calculating with 80% power, a two-sided 99.3% CI, a non-inferiority margin of 1.5% and a 5% drop-out rate, 2119 women need to be randomised to each arm induced with either balloon catheter or oral misoprostol to assess efficacy of either method in the different IOL settings.

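### Table 3 identifies delivery-related hysterectomy only by codes that Table 2 uses for caesarean section, so a correctly coded hysterectomy after vaginal birth is scored as no event

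*Protocol article*

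**What the plan says.** Table 3 of the protocol article lists the outcome "Hysterectomy in connection with delivery" as a yes/no variable. Its description is "ICD-10 O82.2, Procedure code MCA33". The only source is SPR, and there is no tick box. The row belongs to a block headed "Further outcomes for the mother within 12 weeks from delivery if not specified otherwise".

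Table 2, under primary outcome 2, identifies caesarean section by "Tick box ICD-10 O82 Procedure code MCA00, MCA10, MCA20, MCA30, MCA33, MCA96". It identifies vaginal delivery by a tick box, ICD-10 O80 and O81, and "Procedure code MAF00, MAF10, MAF96, MAC23 MAE00, MAE03, MAE20, MAE96".

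The Power calculation section supplies the mode-of-delivery figures: "The vaginal delivery rate was 88% in a group of women fulfilling the eligibility criteria", and "Assuming a vaginal delivery rate of 90% in the outpatient arm".

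**The concern.** The label and the code list describe different events. The label covers hysterectomy linked to any birth. The codes describe a hysterectomy only where the woman is also recorded as a caesarean case. A woman who delivers vaginally and then has a hysterectomy, for example for haemorrhage, would appear in the results as not having had one.

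Two things are at stake. First, a reader of the results would take the count as covering all births, when it covers the minority delivered by caesarean. Second, whether an event can be seen depends on mode of delivery. That is determined after randomisation and is itself the second primary outcome. If the arms differ in caesarean rate, they also differ in the share of women in whom a hysterectomy can be recorded.

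**Working it through.** **Step 1: compare the code sets.**

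| Row | ICD-10 | Procedure codes |
|---|---|---|
| Hysterectomy (Table 3) | O82.2 | MCA33 |
| Caesarean (Table 2) | O82 | MCA00, MCA10, MCA20, MCA30, MCA33, MCA96 |
| Vaginal delivery (Table 2) | O80, O81 | MAF00, MAF10, MAF96, MAC23, MAE00, MAE03, MAE20, MAE96 |

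- MCA33 stands by name in both the hysterectomy and the caesarean rows.
- O82.2 is a subcode of O82. Table 3 uses the neighbouring subcode O82.1 for "Emergency or crash caesarean section", so the article itself treats this family as caesarean codes.
- Neither hysterectomy code appears among the vaginal-delivery codes.

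The hysterectomy codes are therefore wholly contained in the caesarean codes. No other row of Table 3 captures hysterectomy.

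**Step 2: follow a hysterectomy after vaginal birth through the rules.**

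- Coded correctly, it carries neither O82.2 nor MCA33, and Table 3 scores it as no event.
- Coded with O82.2 or MCA33 all the same, Table 3 scores it as an event, but the caesarean row of Table 2 is met as well, in conflict with her vaginal delivery in primary outcome 2.

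Neither route records both the hysterectomy and the mode of delivery correctly.

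**Step 3: how many women this concerns.** The inputs are 8891 randomised, 5% drop-out, and vaginal delivery rates of 88% and 90%, all from the Power calculation section.

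- Evaluable women: 8891 × 0.95 = 8446
- At 88%: 8446 × 0.88 = 7432
- At 90%: 8446 × 0.90 = 7601
- Women in whom the outcome can register under correct coding: 8446 − 7601 = 845 to 8446 − 7432 = 1014

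These are counts of women, not of missed events.

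**Step 4: what can be said about missed events.** Let *v* be the share of vaginal births, and let *k* be the hysterectomy risk after caesarean divided by the risk after vaginal birth. The share of hysterectomies missed is

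*v* / [*v* + (1 − *v*) × *k*].

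If *k* = 1, the share missed equals *v*, that is 88% to 90%. As *k* grows, the share falls towards zero. The article gives neither *k* nor an overall hysterectomy rate, so neither the share nor the number missed can be pinned down.

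**The case against.** The strongest reply is that this is one row among many. Table 3 also lists maternal death, uterine rupture, cardiac arrest, obstetric shock, intensive care admission, embolism, stroke, sepsis, bleeding above 1000 mL and transfusion, none of which is identified through caesarean codes. A haemorrhage or rupture leading to hysterectomy after vaginal birth has its own row. This stands: the gap is in one variable, and maternal safety as a whole is not left unobserved.

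A reader might infer a definite bias. With caesarean rates of 12% and 10%, countable events would stand in the ratio 0.10/0.12 = 0.83 even if the true risk ratio were 1. The document does not support that figure as a result. It needs hysterectomy risk to be unrelated to mode of delivery, and nothing in the article says so. If the risk lies mainly in caesarean births, few events are missed, and a ratio below 1 would partly reflect a real difference. The 12% is also an inference: the article gives 88% for a register population and does not state an inpatient-arm rate. It uses the 88% and 90% for the method-specific efficacy sample size, not for the 8891.

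A reader might also infer that a hysterectomy after vaginal birth can never be counted. Table 3 scores by code, so a case carrying O82.2 or MCA33 would count. The exclusion holds under correct coding only.

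It can also be said that definitions may be settled in the statistical analysis plan (SAP). The footnote to Table 3 leaves to it which variables are secondary and which exploratory. It does not defer the definitions, and the code list here is stated, not omitted.

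**Conclusion.** The point holds as a mismatch between label and definition. The containment of the hysterectomy codes in the caesarean codes can be read directly from Tables 2 and 3 and rests on no assumption about rates. Under correct coding, the outcome cannot register in the roughly 7,430 to 7,600 of 8,446 evaluable women expected to deliver vaginally. That range takes the 88% register figure, the 90% outpatient assumption and the 5% drop-out as given.

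The number of missed events is unknown. Because capture depends on a post-randomisation outcome, the comparison between arms can be distorted, but the size of the distortion cannot be derived from the article.

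The consequence is limited: this is a rare secondary or exploratory maternal safety variable, and no primary analysis or sample size depends on it. It is still worth correcting. Maternal safety variables are among the stated aims, and with a rare outcome a few missed cases can change what is reported.

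**What to change.** Score any hysterectomy within the Table 3 maternal window, 12 weeks from delivery, whatever the mode of delivery. Keep O82.2 and MCA33 in the list, and add the procedure codes for hysterectomy performed separately from caesarean section. Add the National Patient Register as a source. If the words about connection with delivery are meant to set a narrower window than 12 weeks, state that window in the row.

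At minimum, relabel the variable as caesarean hysterectomy, so that the reported count is read for what it is.

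The cost is one table row and a longer code list. No new data source is needed: the Data collection section already includes the National Patient Register, and Table 3 uses it for cardiac arrest, stroke, intensive care admission and maternal readmission. Recruitment is planned to run to 31 December 2028 and the SAP is to be set before data lock, so the change can be made before any analysis.

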#### Procedures and follow-up

The trial intervention is IOL outside of a hospital setting. For IOL due to PROM, the method of cervical ripening and whether the setting will be outpatient or inpatient is set for the first 24 hours. For IOL due to other indications, these details are specified for the first 48 hours. Thereafter, all participants are treated according to clinical routine at their hospital. Usually, IOL will proceed with oxytocin infusion in case of PROM and amniotomy and subsequent oxytocin infusion in women with intact membranes.^29^

Women randomised to inpatient IOL are monitored according to local clinical routine. Women randomised to outpatient IOL return home or to a patient hotel defined as a facility without access to medical surveillance. Participants receive oral and written information on how to proceed with IOL, when and whom to call and when to return to the hospital. Women have access to a 24/7 telephone line staffed by qualified midwives based at the maternity hospital. Women randomised to outpatient IOL receive detailed oral and written instructions to contact the hospital (and refrain from further intake of oral misoprostol) at start of contractions, in case of PROM (if PROM was not the indication for IOL), when the balloon catheter is expelled, sudden change/decrease in foetal movements, vaginal bleeding, abdominal pain, fever and/or feeling unwell, and in case of IOL due to PROM: any change in amniotic fluid colour. These women are counselled to come to the hospital for a clinical evaluation. Women are also encouraged to call in case they feel unsure about anything.

If labour does not start and no complication occurs, women in the outpatient group return for assessment after 24 hours (12 hours in case of IOL with a double balloon (Cook) catheter due to conformité européenne (CE) marking for 12 hours use only) for clinical assessment including vaginal examination of the cervix, blood pressure and CTG. Women induced due to PROM are admitted to the hospital at the latest 24 hours after start of IOL. Women induced due to other indications and a normal assessment may return home/to the patient hotel for continued cervical ripening for another 24 hours if needed.

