**Primary outcome 1 is a composite variable for severe child morbidity and mortality including any of the following:**			
Stillbirth defined as intrauterine foetal death of a fetus that was alive at time of randomisation	Dichotomous (yes, no)	Tick box, ICD-10 O36.4	SPR
Neonatal death of a live born child that dies days 0–27, not including accidents or lethal malformation not known before randomisation	Dichotomous (yes, no)	SNQ 2101, 2103	SNQ, SCB, the Cause of Death Register
Apgar score <4 at 5 min	Dichotomous (yes, no)	SNQ 421, SPR “Apgar 5”	SNQ, SPR
pH <7.00 or base deficit >15 mmol/L in the umbilical artery	Dichotomous (yes, no)		SNQ, SPR
Hypoxic ischaemic encephalopathy I–III	Dichotomous (yes, no)	ICD-10 P91.6 or P91.0 or tick box	SNQ
Intracranial haemorrhage	Dichotomous (yes, no)	ICD-10 P10, P52	SNQ
Neonatal convulsions	Dichotomous (yes, no)	ICD-10 P90	SNQ
Therapeutic hypothermia	Dichotomous (yes, no)	Procedure code DV034	SPR, SNQ
Meconium aspiration syndrome	Dichotomous (yes, no)	ICD-10 P24.0	SNQ, SPR
Mechanical ventilation within first 72 hours	Dichotomous (yes, no)	Procedure code DG021, DG022, DG002	SNQ
Neonatal pneumonia	Dichotomous (yes, no)	ICD-10 P23	SNQ
Neonatal sepsis	Dichotomous (yes, no)	ICD-10 P36	SNQ
NICU admission >48 hours duration	Dichotomous (yes, no)		SNQ

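### Table 3 gives the 48-hour vaginal delivery outcome a 24-hour rule and defines three of the 13 safety-composite components differently from Table 2; the neonatal-death exclusion also differs between Table 2 and the text

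*Protocol article*

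**What the plan says.** **Timed vaginal delivery (Table 3).** Two consecutive rows are labelled "Vaginal delivery within 24 hours (VD24" and "Vaginal delivery within 48 hours (VD48". Both carry the same description: "As above within 24 hours after start of induction".

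**Components of the safety composite.** The first block of Table 3 opens by stating that the variables making up the primary safety composite will also be examined individually, as exploratory analyses. Table 2 and the Primary outcomes section define that composite. The places that differ are these:

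- Encephalopathy is "Hypoxic ischaemic encephalopathy I–III" in Table 2, with codes P91.6 or P91.0 or a tick box. It is "Hypoxic ischaemic encephalopathy II–III" in Table 3, with P91.6B or C or a tick box. The Primary outcomes text agrees with Table 2 (grades 1 to 3).
- Therapeutic hypothermia is identified by "Procedure code DV034" in Table 2 and by "ICD-10 P80.8, P80.9, DV034" in Table 3.
- Neonatal death has one set of exclusions in the Primary outcomes text, another in Table 2 and a third in Table 3.
- Stillbirth has a tick box and code O36.4 in Table 2, and the code only in Table 3.
- Severe birth asphyxia (P21.0) has a row in this block of Table 3. It is in neither Table 2 nor the Primary outcomes text.

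The footnote to Table 3 leaves to the final statistical analysis plan which variables are secondary and which exploratory. It does not say that the definitions are still open.

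**The concern.** Outcome tables with register codes are what a programmer works from. If Table 3 is followed literally, VD48 is a copy of VD24, and vaginal deliveries after 24 and up to 48 hours from the start of induction count in neither variable.

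The second issue is interpretation of the safety result. The composite combines deaths with events such as a neonatal intensive care stay of more than 48 hours, so a reader needs the component counts to see what drives any difference between the groups. Those counts help only if they use the definitions that produced the composite. Where a definition changes between the tables, the component count and the composite cannot be reconciled.

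The third issue concerns the primary outcome directly. Neonatal death is a component of the composite, and the article states its exclusions in two ways in the places that define the composite.

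**Working it through.** No sample size, power or error rate enters this point, so there is no figure to reproduce. The check is a row-by-row comparison.

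**1. VD24 and VD48.** The labels say 24 and 48 hours; the descriptions both say 24. As written, the set of women with VD48 equals the set with VD24. Table 3 also lists time from start of induction to delivery as a continuous variable, and Table 2 records mode of delivery, both from the Swedish Pregnancy Register. VD48 can therefore be derived as a vaginal delivery with a time to delivery of at most 48 hours.

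**2. The 13 components, Table 2 against Table 3.**

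| Component | Table 2 | Table 3 | Result |
|---|---|---|---|
| Encephalopathy | I–III; P91.6 or P91.0 or tick box | II–III; P91.6B or C or tick box | differs in substance |
| Therapeutic hypothermia | DV034 | P80.8, P80.9, DV034 | differs in substance |
| Neonatal death, days 0–27 | excludes accidents, and lethal malformation not known before randomisation | excludes accidents only | differs in substance |
| Stillbirth | tick box, O36.4 | O36.4 | differs in ascertainment only |
| Apgar <4 at 5 min; pH or base deficit; intracranial haemorrhage; convulsions; meconium aspiration; ventilation; pneumonia; sepsis; intensive care >48 hours | – | – | nine rows match |

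Count: 9 match + 3 differ in substance + 1 differs in ascertainment = 13. Severe birth asphyxia is a further row in the Table 3 block and lies outside the composite.

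**3. What the differences do to a single child.**

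- A child whose only event is grade I encephalopathy counts in the composite but has no encephalopathy row in Table 3. This assumes that the tick box there is limited to grades II–III, which the article does not say.
- A child with only P80.8 or P80.9 counts in the Table 3 hypothermia row but does not meet the Table 2 criterion.
- A death from a lethal malformation not known before randomisation counts as a neonatal death in Table 3 but not in Table 2.
- A child with P21.0 alone counts in a row of the component block but does not enter the composite on that ground.

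In the last three cases the child may still enter the composite through another component.

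**4. Neonatal death in the definition of the primary outcome.**

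| Place | Lethal malformation | Accidents |
|---|---|---|
| Primary outcomes text | excluded, no qualifier | not mentioned |
| Table 2 | excluded if not known before randomisation | excluded |
| Table 3 | not excluded | excluded |

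The text and Table 2 therefore classify two kinds of death differently: accidental deaths, and deaths from a lethal malformation already known at randomisation. Table 1 bars women with known foetal malformations affecting delivery or the immediate care of the newborn, so the second kind should be uncommon. That leaves accidents as the main difference between these two places, and malformations discovered later as the main difference between Table 2 and Table 3.

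**The case against.** **VD48 is an obvious copying slip.** This stands. The label and the collected time to delivery leave no doubt about the intent. A reader might infer that the trial has no 48-hour outcome or will lose data on it; the article does not support that. Nor does it support treating VD48 as the measure matched to the ripening period. The Procedures and follow-up section says "For IOL due to other indications, these details are specified for the first 48 hours", which concerns setting and method of ripening. Amniotomy or oxytocin usually follows, so delivery by 48 hours is a different quantity, and the article gives VD48 no such role.

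**Encephalopathy II–III may be deliberate.** This stands as a possibility. Label and codes change together, and the block also holds severe birth asphyxia, so it may mix components with added outcomes. On that reading the I–III row is missing rather than altered. Either way, the block does not deliver the breakdown that its opening sentence announces.

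**Most components agree.** Correct: nine of 13 match, and stillbirth differs only by a tick box. A reader might infer that the component table as a whole fails to decompose the composite. The mismatch in substance is confined to three rows.

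**The primary analysis is unaffected.** This is almost right. Table 3 changes neither the composite nor the margin, power or error rate, and the component analyses are labelled exploratory. The exception is neonatal death, where the two places that define the composite disagree with each other.

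**The final analysis plan can settle it.** It can, and it is to be set before data lock. But these rules are stated in the article, not left out of it, and the Table 3 footnote defers only the split between secondary and exploratory.

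**Conclusion.** Wrong as written, and worth correcting. The VD48 description contradicts its label. Three of 13 component definitions in Table 3 differ in substance from Table 2, one differs in ascertainment, and one row does not belong to the composite. The exclusions for neonatal death are stated in three ways, two of them in the definition of the primary outcome.

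Apart from the neonatal-death rule, the effect is limited to secondary and exploratory outcomes and to interpretation of the composite. The number of children who would be classified differently cannot be derived, because the article gives no frequencies for grade I encephalopathy, for P80.8 or P80.9 alone, or for the deaths in question. The conclusion rests on the tables as printed and on no outside knowledge of what the codes mean.

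**What to change.** 1. In Table 3, change the VD48 description to 48 hours counted from the start of induction.
2. In the component block of Table 3, use the Table 2 definitions, codes and sources, including encephalopathy I–III, DV034 alone for therapeutic hypothermia, and the stillbirth tick box.
3. If encephalopathy II–III and severe birth asphyxia are wanted, list them separately as additional outcomes outside the composite.
4. Choose one exclusion rule for neonatal death, covering both malformations and accidents, and state it identically in the Primary outcomes text, Table 2 and Table 3.

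The cost is a correction to two tables and one sentence, carried into the final analysis plan before the registers are extracted. There is time: recruitment is planned to run to 31 December 2028 and the final plan has not been set. No additional data collection is needed for VD48 or for the Table 2 definitions.
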